### Sample size

According to a literature review [9, 34–42], 97 % and 90 % of success is expected for P and C dentin excavation strategies, respectively. A total of at least 464 patients would be needed for a bilateral test with an alpha risk of 5 % and a power greater than 80 %, supposing at 1 year 10 % of patients lost to follow-up as a ‘not to exceed’ value (calculated by nQuery Advisor 7.0) [43–45].

With the expected recruitment of each investigator, in order to reach the target sample size and respect the inclusion period of 18 months, this trial involves 15 centers. To encourage recruitment, the main investigator sends an encouraging text message after each inclusion and the center recruitment appears on the main page of the randomization website.

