With pulp exposure < 2 mm^2^ after C excavation, the exposed pulp is irrigated with chlorhexidine. Following hemostasis (within 5 minutes), a tricalcium silicate cement (Biodentine™, Septodont, Saint Maur des Fossées, France) is applied according to the manufacturer’s instructions. After complete cement setting (within 15 minutes), the cavity is restored following the same clinical procedures as for cases without pulp exposure.

With pulp exposure > 2 mm^2^ and/or no hemostasis, a root canal treatment is performed, and the case is considered a failure for randomization 1 but not randomization 2.

Cases undergo randomization 2 to determine the adhesive system: Clearfil™ SE Bond (Kuraray Europe) or Clearfil™ SE Protect (Kuraray Europe) (i.e., TA and AA, respectively). Enamel and dentin are prepared according to the manufacturer’s instructions. The tooth is restored by using the Gradia® Direct Flo and Gradia® Direct Posterior composite resin (GC Europe N.V., Leuven, Belgium) in accordance with the manufacturer’s instructions and if necessary a matrix system (Kerr Restauration, Bioggio, Switzerland). The photo-polymerization steps involve use of a LED curing light (Demi™ Ultra, Kerr Restauration, Bioggio, Switzerland). Then, a bite-wing radiograph is taken as a control.

Various strategies are implemented to improve adherence to intervention protocols: the investigator must submit the fluorescence image obtained after caries removal as well as the control radiograph to the randomization website. He must also indicate the adhesive applied.

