### Statistical methods

The statistical unit for analysis will be the tooth. Only one tooth per patient will be included and treated according to the protocol. The demographic and clinical characteristics of patients and treated teeth will be described for both treatment arms with mean and SD or median and interquartile ranges for quantitative variables and number of subjects, and percentages for qualitative variables. The analyses will be performed according to the intention-to-treat principle.

To evaluate the primary objective, the probability of success in arms P and C at 1 year will be calculated and compared by Fisher’s exact test. The probability of success for each arm (0 for treatment failure and 1 for success, at 1 year) will be assessed by a hierarchical logistic model. This model accounts for the correlation related to the hierarchical structure of the data (several patients treated by one practitioner) as well as any possible inter-practitioner heterogeneity. The model will be adjusted on the type of adhesive (arm AA or TA) and on prognostic factors accounted for in the minimization scheme. If necessary, other adjustment factors might also be considered. In cases of patient non-compliance with follow-up visits, the last investigator’s assessment will be used in the analysis, if there is one.

All analyses related to the primary objective (Fisher’s exact test and the modeling approach) will initially include all patients with an available primary outcome as modified ITT. The number of patients to be included has been increased to account for missing outcomes. Then, three sensitivity analyses will be performed: the first according to the maximal bias approach (missing data considered as “success” in arm C and as “failure” in arm P), the second considering all missing data as successes, and the third considering all missing data as failures.

For the secondary objectives comparing efficacy (as defined for the primary objective) at 1, 2, and 3 years and between arm AA and arm TA at the three different times, similar analyses to those used for the primary objective will be performed. The probability of success for each criterion will be assessed and compared between arms by using the hierarchical logistic model described previously.

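### The plan compares each FDI criterion with the fully adjusted hierarchical logistic model, but its own success rates leave only about five failures per criterion at 1 year

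*Protocol article*

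**What the plan says.** The Outcome measures section counts a tooth as a success when all five selected FDI criteria score 3 or less; a score of 4 or 5 on any one makes it a failure. The Statistical methods section gives the composite a Fisher's exact test and a hierarchical logistic model. That model has a practitioner level and is adjusted for adhesive and for the factors used in the minimization. The Randomization section lists these as investigator, age group, lesion type, lesion location and pulp exposure. The covariate list is left open: "If necessary, other adjustment factors might also be considered".

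After the paragraph's text on the 1-, 2- and 3-year comparisons and on antibacterial (AA) versus traditional (TA) adhesive, the plan adds: "The probability of success for each criterion will be assessed and compared between arms by using the hierarchical logistic model described previously". For the separate criteria this model is the only method named.

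The expected event rates are in the Sample size section, for the composite only: "97 % and 90 % of success is expected for P and C dentin excavation strategies, respectively". The Intervention section adds a kind of failure that does not depend on an FDI score. With a large pulp exposure or no hemostasis, "a root canal treatment is performed, and the case is considered a failure for randomization 1".

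**The concern.** A model that can be fitted to the composite may not be fittable to a fifth of its events. If an arm has no failure on a criterion, the likelihood keeps rising as the arm coefficient moves towards infinity, whatever values the other parameters take. A practitioner random intercept does not change that. Even when both arms have a failure, a handful of events cannot support six or more slopes and a variance component.

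At stake is the breakdown of the composite. A reader would use the criterion results to see whether a difference between P and C lies in pulp and apical outcomes or in the restoration itself. As specified, some of those results could be infinite, non-convergent or dependent on software defaults.

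**Working it through.** **Inputs from the protocol article**
- Success 97% (P) and 90% (C), so failure 3% and 10% (Sample size).
- "A total of at least 464 patients would be needed for a bilateral test with an alpha risk of 5" per cent, with "a power greater than 80" per cent and "supposing at 1 year 10 % of patients lost to follow-up" (Sample size).
- Allocation 1:1 (Trial design); five criteria (Outcome measures); Fisher's exact test (Statistical methods).

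**Step 1: reproduce 464.** The exact power of the two-sided Fisher test at 3% against 10% failure is 79.9% with 208 per arm and 80.1% with 209. Allowing for loss, 209/0.9 = 232.2, or about 232 per arm and 464 in total. The stated figure is reproduced, and 209 evaluable per arm is the plan's own working number.

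**Step 2: failures on the composite at 1 year.** P: 209 × 0.03 = 6.27. C: 209 × 0.10 = 20.9. Total 27.2.

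**Step 3: failures per criterion.** The documents give no rate per criterion. *Assumption:* even split, one failed criterion per failed tooth.
- P: 6.27/5 = 1.25. C: 20.9/5 = 4.18. Total 5.4.
- Slopes: arm, adhesive, age group (at least one), lesion type, location, pulp exposure = at least 6. Events per slope: 5.4/6 = 0.9. For the composite the ratio is 27.2/6 = 4.5.
- There are 15 centers, so at least 15 practitioners if each center has one. That is 5.4/15 = 0.36 events per center, and most centers would have none.

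**Step 4: chance of no finite arm effect, P versus C at 1 year.**
- No P failure on a given criterion: (1 − 0.03/5)^209 = 0.994^209 = 0.284.
- No C failure: (1 − 0.10/5)^209 = 0.98^209 = 0.015. Either arm: 1 − 0.716 × 0.985 = 0.295.
- Expected number of the five fits with no P failure: 5 × 0.284 = 1.42.
- At least one of five, treating criteria as independent: 1 − 0.716^5 = 0.81.

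**Step 5: range over the assumption.**

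| Split of failures | P failures per criterion | Chance of zero P failures on a criterion | At least one of five |
|---|---|---|---|
| Even, 1 criterion per failed tooth | 1.25 | 28% | 81% |
| Even, 1.5 criteria | 1.9 | 15% | 56% |
| Even, 2 criteria | 2.5 | 8% | 34% |
| Even, 3 criteria | 3.8 | 2% | 11% |
| Uneven, no overlap: 30/30/20/10/10% | 0.6 to 1.9 | 15% to 53% | 89% |
| Uneven, no overlap: 50/20/10/10/10% | 0.6 to 3.1 | 4% to 53% | 93% |
| Uneven, no overlap: 40/30/15/10/5% | 0.3 to 2.5 | 8% to 73% | 94% |

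Independence is a rougher approximation in the overlap rows.

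**Step 6: the full covariate set.** A simulation of 1,000 trials per setting fitted only the fixed-effects part: seven slopes (three age groups assumed), assumed covariate prevalences and no true covariate effects. Some coefficient, not necessarily the arm effect, was non-finite in about 79% of fits with one failed criterion per tooth, 45% with two and 23% with three.

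**Step 7: AA versus TA.** The average failure rate per criterion is (0.03 + 0.10)/2/5 = 0.013. That gives 209 × 0.013 = 2.7 failures per arm and a zero in a given arm with probability 0.987^209 = 0.065.

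**Step 8: effect of T0 root-canal failures.** If half of the C failures were of this kind (an assumption) and had no criterion score, C failures per criterion would be 209 × 0.05/5 = 2.1 and total events about 3.3. The chance of a zero in either arm would be 1 − (1 − 0.284)(1 − 0.99^209) = 1 − 0.716 × 0.878 = 0.37. For AA versus TA the figures would be 1.7 failures per arm and a 19% chance of zero in a given arm.

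**The case against.** The strongest reply is that the count per criterion is not in the documents. The stated rates are for the composite, and the criteria can fail together, for example marginal adaptation with caries recurrence. With two or three failed criteria per tooth, the chance of an infinite P-versus-C effect drops to 8% or 2%. This stands, and it is why the result is given as a range. Uneven splits without overlap move it the other way.

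A reader might infer that most criterion fits would fail. The documents do not support that. Even under the even split about 72% of the 1-year P-versus-C fits have at least one P failure, the adhesive fits are less exposed, and the 2- and 3-year fits should be too if failures accumulate.

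The article does not name an estimator, and a sparse-data fallback may be in an analysis plan that is not shown. The absence of a fallback is therefore not the point. The point is that the article fixes one adjusted model for every criterion, and its own rates do not support that model. The 28% does assume ordinary maximum likelihood.

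A reader might also infer that root-canal failures at T0 go unreported or are the most important component. Neither follows. The Outcome measures section already lists the number of endodontic treatments per arm, to be described, and nothing ranks the components. What remains is narrower: these teeth fail by rule rather than by an FDI score, so a breakdown by criterion alone need not add up to the composite.

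Finally, the open option to add covariates is written for the composite model. It matters here only because the criterion analysis inherits that model.

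**Conclusion.** The concern holds for the criterion-level analysis. On the plan's own rates the composite yields about 27 failures at 1 year. Under an even, non-overlapping split about 5.4 fall on each criterion, against at least six slopes and a practitioner variance, so the specified model is over-parameterised. With ordinary maximum likelihood about 28% of the 1-year P-versus-C criterion fits would have no finite arm effect. The range is about 2% (three failed criteria per tooth) to 73% (rarest criterion under an uneven split). At least one of the five would be affected in about 81% of trials under the even split. For AA versus TA the chance of zero failures in a given arm is about 6%.

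This is a weakness of a secondary component analysis. It would be wrong to read it as a threat to the primary result: Fisher's exact test on the composite is unaffected, and the sample size of 464 is reproduced with that test.

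**What to change.** Replace the criterion-level sentence. For each FDI criterion and time point, report the number of failures and the number assessed in each arm, and the risk difference with an exact or score 95% CI. If a model is wanted, use Firth-penalised logistic regression with arm as the only covariate. Keep the adjusted hierarchical model for the composite.

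In the P-versus-C component table, show root-canal treatment at T0 as its own line, so that every failure on the composite can be traced to a listed component. A tooth may appear on more than one line, and the table should say so.

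The change is to analysis wording only, with no extra data. The price is that criterion comparisons lose covariate and practitioner adjustment, which about five events per criterion could not support.

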## Methods/design

### Trial design

The Standard Protocol Items: Recommendations for Interventional Trials (SPIRIT) guidelines [33] have strictly been followed in the planning of this trial (Additional file 1).

This trial is a multicenter intention-to-treat randomized controlled superiority trial with parallel arms. Analysis of results will be performed according to the intention-to-treat principle. For the primary objective, only patients are blinded to the allocated intervention (partial or complete caries removal). For the secondary objective (type of adhesive), both patients and investigators are blinded. Outcome examiners and data analysts are always blinded.

Two successive randomizations are performed (allocation ratio 1:1): first, for the type of excavation (P versus C) and second, for the adhesive system (AA) versus TA. The second randomization is not performed for teeth requiring endodontic treatment after the first randomization.

The possible combinations of interventions are in Fig. 1, the flow diagram is mentioned on Table 1 and the flow chart of the study is in Fig. 2.

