### Outcome measures

Cases are considered successful if each of the following five FDI World Dental Federation (FDI) criteria has a final score ≤ 3: material fracture and retention, marginal adaptation, radiographic examination (including apical pathologies), postoperative sensitivity and tooth vitality, and recurrence of carious lesions [48, 49]. A score of 4 or 5 indicates that reintervention is necessary and, therefore, the case is classified as a failure in the context of the study. Criteria are scored at 1, 2, and 3 years’ postintervention by two blinded independent trained evaluators. Study assessing the agreement between evaluators for FDI criteria is ongoing. In cases of emergency visits, FDI criteria will be scored by the investigator.

For the primary objective (P versus C excavation) and the main secondary objective (AA versus TA), the outcome will be the success (yes/no) at 1 year, as defined previously.

For the first secondary objective (identification of factors predicting success at 1 and 3 years), the following candidate factors will be investigated: postoperative pain, patient age, type of carious lesion (primary or secondary), location of the carious lesion, and pulp exposure.

For the second secondary objective (description of the consequences of treatment failure and side effects per treatment arm), the following events will be considered: total number of needed visits, number of endodontic treatments, and number of avulsions.

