Candidate factors for subgroup analyses are patient age, type of carious lesion (primary or secondary), caries risk, lesion location, and pulp exposure. Subgroup analyses will be performed globally, then stratified by type of removal (C and P) and adhesive (AA and TA). In the model analysis, the interaction between a specific factor and the type of removal (arms C versus P) or the adhesive used (arms AA versus TA) will also be considered by its clinical relevance and in the descriptive analyses. The consequences of failure and side effects between arms will be assessed by a descriptive approach (range, median, and quartiles for quantitative variables, number and percentage for qualitative variables).

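### Quartiles and range alone are a poor summary of the number of visits: at the planned 1-year failure rates the quartiles are expected to coincide in the two excavation arms

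*Protocol article*

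**What the plan says.** The article's Objectives section includes a descriptive secondary objective on what follows from treatment failure, and on side effects, in each arm. Outcome measures lists the events to be considered: "total number of needed visits, number of endodontic treatments, and number of avulsions". Statistical methods says these will be "assessed by a descriptive approach (range, median, and quartiles for quantitative variables, number and percentage for qualitative variables". No mean is named for this objective, although the same section allows mean and SD as an alternative for baseline characteristics.

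Table 1 gives every patient the same five visits (selection, randomization, and years 1, 2 and 3), plus emergency visits that may occur at any time up to 3 years. The Sample size section states that "97 % and 90 % of success is expected for P and C dentin excavation strategies, respectively", which implies failure rates of 3% and 10%. These are the planning values for the 1-year outcome.

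**The concern.** With one tooth per patient, endodontic treatment and avulsion are yes/no events, so the rule for quantitative variables applies in practice to visits. If most patients attend only the schedule and a small minority have extra visits, the visit count is a constant plus a count made up mostly of zeros. Quartiles of such a variable do not respond until about a quarter of an arm has an extra visit. The minimum will usually be the schedule, and the maximum is set by one patient.

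At stake is whether the visits line of the table shows the difference in burden between the strategies. The Discussion names time and cost among the considerations that would favour wider adoption of partial excavation. These are not trial objectives, but the visit count is the listed variable that bears most directly on time.

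**Working it through.** **Inputs.** Failure 3% (P) and 10% (C) from Sample size; "A total of at least 464 patients would be needed"; "supposing at 1 year 10 % of patients lost to follow-up"; 1:1 allocation from Trial design; five scheduled visits from Table 1.

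**The plan's own figure.** For a "bilateral test with an alpha risk of 5 % and a power greater than 80" %, with the arms "will be calculated and compared by Fisher’s exact test", exact enumeration gives 79.9% power at 208 per arm and 80.1% at 209. Two arms of 209 make 418, and 418 / 0.9 = 464.4, against the stated 464. The sample size reproduces, and 209 evaluable teeth per arm is a fair basis for what follows.

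**Step 1: when does the upper quartile move?** With 209 ordered values, the upper quartile is the 157th (0.75 × 208 + 1 = 157). It exceeds the scheduled number only if at least 209 − 156 = 53 patients have an extra visit. The expected numbers of failures are 0.03 × 209 ≈ 6 (P) and 0.10 × 209 ≈ 21 (C). If only failures add visits, the chance is the binomial tail Pr(X ≥ 53 | n = 209, p):

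| Share with an extra visit | Pr(X ≥ 53) |
|---|---|
| 10% | 1.7 × 10⁻¹⁰ |
| 15% | 6.6 × 10⁻⁵ |
| 20% | 0.035 |
| 27.1% | 0.74 |

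At the 1-year rates, the median and both quartiles therefore equal the schedule in both arms.

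**Step 2: what is hidden.** If a failure brings k extra visits on average, the true C-minus-P difference is (0.10 − 0.03) × k = 0.07k. For k from 1 to 3 (assumed), that is 0.07 to 0.21 visits per patient.

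**Step 3: visits unrelated to failure.** Assume 1 + Poisson(1) extra visits per failure (mean 2, so a true difference of 0.07 × 2 = 0.14) and Poisson background visits with mean b in both arms. The share of an arm with any extra visit is 1 − (1 − f) × exp(−b), where f is the failure rate. The last column comes from 4,000 simulated trials per row, 209 per arm:

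| b | P, any extra | C, any extra | All three quartiles equal |
|---|---|---|---|
| 0 | 3.0% | 10.0% | 100% |
| 0.05 | 7.7% | 14.4% | 100% |
| 0.10 | 12.2% | 18.6% | 99% |
| 0.20 | 20.6% | 26.3% | about 36% |
| 0.25 | 24.5% | 29.9% | about 42% |
| 0.30 | 28.1% | 33.3% | about 83% |

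The true difference is 0.14 in every row. The quartiles differ mainly when C lies above the 25% mark and P below it, and the upper quartile then jumps by a whole visit. Once both arms are above it, the quartiles mostly agree again.

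**Step 4: three years.** A constant yearly rate (assumed) gives 1 − 0.97³ = 8.7% for P and 1 − 0.90³ = 27.1% for C. If only failures add visits, C's upper quartile moves in about 74% of trials, while the chance for P is about 10⁻¹². With two extra visits per failure, the true difference is (0.271 − 0.087) × 2 ≈ 0.37 visits, but the upper quartile shows either none or, almost always, exactly one.

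**Step 5: the range.** With no background visits, the minimum and maximum both matched across arms in only about 24% of simulated trials. The range usually differs, but because of one patient per arm.

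**The case against.** The strongest case against is that this is a descriptive objective in a condensed article, that table layout belongs to the analysis plan, and that nothing forbids adding a mean. The visit distribution is assumed. The article does not say that only failures generate extra visits: emergency visits are not restricted to failures, some patients will miss visits, and modest background rates already make the quartiles differ. Nor does it say that the summary covers all patients. Restricted to failed cases, quartiles would describe visits per failure and the excess of zeros would disappear.

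Much of this stands, and it limits the point. Several stronger readings that a reader might infer are not supported:

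- **That the objective cannot be answered.** Two of its three variables can be shown as number and percentage. For illustration, if every failure were such an event, about 6/208 against 21/208 would be visible at once.
- **That all the planned statistics will be identical.** The range usually differs, and over 3 years the upper quartile may well differ.
- **That a test of visits is missing or underpowered.** The objective is descriptive and calls for no test.
- **That time or cost is a trial objective.** These appear only as a general remark in the Discussion.

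The objection does not remove the narrower point. The article does not leave the summary open: it names the statistics. Where background visits make the quartiles differ, the result is a whole-visit jump that depends on unrelated visits and does not estimate the difference. A summary among failed cases only would not compare visit burden per randomised arm.

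**Conclusion.** The point holds for the visits component alone and is minor. If visits are summarised over all patients and extra visits arise mainly from failures, the median and quartiles are expected to coincide at the 1-year planning rates, against a true difference of 0.07 to 0.21 visits per patient for 1 to 3 extra visits per failure. With unrelated visits averaging up to 0.10 per patient, the quartiles still coincide in 99% to 100% of simulated trials. Beyond that, or over 3 years, the upper quartile may show no difference or a whole visit. The denominator, the visits per failure, the background rate and the constant yearly failure rate are assumptions, not figures from the article. The primary comparison, the sample size, and the reporting of endodontic treatments and avulsions are untouched.

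**What to change.** In Statistical methods, where the analysis of consequences of failure and side effects is described, add for each excavation arm, over all randomised patients:

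- the mean number of visits beyond the schedule;
- the P-minus-C difference in means with a 95% CI (bootstrap or robust), given as description;
- the number and percentage of patients with at least one unscheduled visit.

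Do the same for the antibacterial versus the traditional adhesive among teeth that underwent the second randomization. The range and quartiles can stay as extra description. No formal test or power statement is needed.

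The cost is a sentence or two in the analysis text and a few table lines. No new data are needed.
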